#### Sample size

Sample size is calculated on the basis of complication other than re-rupture. With conservative treatment using this new type of functional bracing we hypothesized a 30% reduction in the absolute risk for complications other than re-rupture. This risk reduction is similar to the risk reduction obtained in the systematic review on open versus conservative treatment by Khan: risk of complications for open repair being 34% [5]. Prospective data on the risk of complications of minimally invasive repair is very scant. The Khan review provides the best empirical estimate for the complication risk associated with surgical repair. Therefore we decided to use this risk estimate of complications of open repair for the sample size calculation. With a one-sided α of 0.05, a statistical power of (1-β) of 0.80, and an attrition rate of 10% we need to randomize at least 36 patients per treatment arm.

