**Methods/Design:**

At least 72 patients with acute Achilles tendon rupture will be randomized to minimally invasive surgical repair followed by functional rehabilitation using tape bandage or conservative treatment followed by functional rehabilitation with use of a functional bracing system. Both treatment arms use a 7 weeks post-rupture rehabilitation protocol. Four hospitals in the Netherlands will participate. Primary end-point will be reduction in complications other than re-rupture. Secondary end-point will be re-rupturing, time off work, sporting activity post rupture, functional outcome by Leppilahti score and patient satisfaction. Patient follow-up will be 12 month.

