#### Data analysis

The study groups will be compared for their baseline characteristics. The number of complications will be calculated for the primary endpoint. Distribution measures will be calculated for the secondary endpoints at the different moments of follow-up. Differences between groups for the number of complications and distribution of other endpoints will be calculated for each outcome measure with a 95% confidence interval. The study groups will be compared with the chi-square test for categorical outcome variables and the independent sample Student *t *test for continuous outcome variables. The dropouts and withdrawals will be summarized and analyzed by treatment groups. A listing of subject with withdrawal with the date and reasons for termination will be provided.

Because we standardised the intevention procedures we do not anticipate important differences between centers. So we do not stratify our primary analysis for center. However, when eventually differences may occur we will explore their effect in a secondary analysis (Mantel-Haenszel). All analysis in SPSS (SPSS Inc, Chicago Illinois).

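### The 36 patients per arm does not follow from the stated one-sided α of 0.05, and that α does not match the planned 95% confidence interval

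*Protocol article*

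**What the plan says.** The Sample size section of the protocol article sets the error rate, power and attrition in one sentence: "With a one-sided α of 0.05, a statistical power of (1-β) of 0.80, and an attrition rate of 10% we need to randomize". The resulting minimum is 36 per arm. The effect is given earlier in the same section: "we hypothesized a 30% reduction in the absolute risk for complications other than re-rupture". The surgical risk is taken as 34%, from a systematic review of open repair, so the comparison is 34% against 4%. The abstract carries the resulting total: "At least 72 patients with acute Achilles tendon rupture will be randomized".

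On the analysis, the Data analysis section says: "The study groups will be compared with the chi-square test for categorical outcome variables". It adds that group differences "will be calculated for each outcome measure with a 95% confidence interval". It names no one-sided test, one-sided bound or 90% interval, and it does not say whether the chi-square p-value is to be read one-sided or two-sided.

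**The concern.** There are two mismatches. First, the sample-size sentence gives every input needed to recompute its result, and the recomputed number is clearly smaller than 36. Second, one-sided 0.05 allows a 5% chance of a false claim in favour of conservative treatment, whereas a 95% interval that excludes zero in that direction allows 2.5%.

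The number of patients is not at risk. What is at stake is the threshold for the primary conclusion. If the protocol does not settle which α governs, a borderline result can be read either way once the data are known. The treatment is open to patients and physicians, and the Randomisation and concealment section acknowledges that examination reveals the allocation. A threshold fixed in advance is a cheap protection in such a trial.

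**Working it through.** **Inputs.** All are from the Sample size section: p1 = 0.34; p2 = 0.34 − 0.30 = 0.04; difference d = 0.30; power 0.80 (z = 0.8416); attrition 10%. The stated α is one-sided 0.05 (z = 1.6449). The two-sided alternative has z = 1.9600.

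**Common terms.** p1(1−p1) + p2(1−p2) = 0.2244 + 0.0384 = 0.2628, square root 0.5126. Mean risk 0.19; 2 × 0.19 × 0.81 = 0.3078, square root 0.5548. d² = 0.09.

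**Formulas, evaluable patients per arm.**
- Unpooled: n = (zα + zβ)² × 0.2628 / d²
- Pooled: n = (zα × 0.5548 + zβ × 0.5126)² / d²
- Continuity-corrected, from the pooled n: n' = (n/4) × [1 + √(1 + 4/(n d))]²

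Each result is rounded up, divided by 0.9 and rounded up again.

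**As stated, one-sided 0.05.**
- Unpooled: 2.4865² × 0.2628 / 0.09 = 18.1, so 19 evaluable and 22 randomised.
- Pooled: (0.9126 + 0.4314)² / 0.09 = 20.1, so 21 and 24.
- Continuity-corrected: (20.07/4) × [1 + √(1 + 4/6.021)]² = 26.3, so 27 and 30.

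The arcsine formula gives 17.4, so 18 and 20. None gives 36.

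**Two-sided 0.05.**
- Unpooled: 22.9, so 23 and 26.
- Pooled: (1.0874 + 0.4314)² / 0.09 = 25.6, so 26 and 29.
- Continuity-corrected: (25.63/4) × [1 + √(1 + 4/7.690)]² = 31.95, so 32 and 32/0.9 = 35.6, i.e. 36. This is the stated figure, and 2 × 36 = 72. Applying attrition as 32 × 1.1 = 35.2 also gives 36.

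**Sensitivity to the rates.** With one-sided 0.05, power 0.80 and continuity correction, 34% vs 3% (the 3% is in the Background) gives 28 randomised, 33% vs 3% gives 29 and 34% vs 5% gives 33. None reaches 36.

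**Power that 36 per arm delivers.** Exact binomial enumeration at 32 evaluable per arm, 34% vs 4%:

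| Test | One-sided 0.05 | Two-sided 0.05 |
|---|---|---|
| Chi-square, uncorrected | 96.4% | 92.1% |
| Chi-square, continuity-corrected | 91.0% | 84.6% |

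**Where the threshold matters** (surgical vs conservative, 32 evaluable per arm):
- 8/32 vs 2/32. Pooled risk 10/64 = 0.156, standard error 0.0908. Continuity-corrected z = (0.1875 − 1/32)/0.0908 = 1.72, so p = 0.043 one-sided and 0.085 two-sided. Fisher's exact test gives 0.041 and 0.082. Without correction, z = 2.07 and two-sided p = 0.039, so both thresholds then agree.
- 5/32 vs 1/32. Uncorrected z = 0.125/0.0729 = 1.72, so p = 0.043 one-sided and 0.086 two-sided; the Wald 95% interval runs from −1.5 to 26.5 percentage points. With continuity correction or Fisher's test this table is not significant under either threshold.

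Discordant tables thus exist with or without correction, but they are different tables. For the uncorrected test, the chance of landing between the thresholds is about 4% at 34% vs 4%. It is about 13 to 14% if the surgical risk is 15 to 20% against 4%. Those lower surgical risks are assumed values, not figures from the protocol.

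**The case against.** Three objections have weight.

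**The cause is not proved.** A reader might infer that one-sided is definitely the wrong word. The documents do not establish that: no formula or correction is named, and the hypothesis is directional, so a deliberate one-sided α is plausible. One-sided 0.05 with 90% power can also lead to 36. For 34% vs 4%, the unpooled formula with correction gives 31.3, so 32 evaluable and 36 randomised. For 34% vs 3%, the pooled formula with correction gives 31.07, with the same result. Both contradict the stated power of 0.80, and the second also changes the conservative rate to 3%. The two-sided route changes only the sidedness, which makes it the more likely explanation and no more than that.

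**There is no second declared decision rule.** A reader might infer that the protocol sets two competing primary rules, or that the chi-square test itself contradicts a one-sided α. Neither follows. The sidedness of the test is not stated, and a 2×2 chi-square can be converted to a directional p-value. The 95% interval is planned for every outcome and is not declared to be the primary criterion. What stands is narrower: one α is declared, and the only interval planned does not match it.

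**The error is in the safe direction.** This is correct. The plan asks for at least 36 per arm, more than its stated inputs require. That wording does not repair the calculation, however, because 36 is presented as the minimum needed.

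**Conclusion.** The point holds in a limited form. On the stated inputs the requirement is 22 to 30 randomised per arm by the three usual formulas, against 36 stated. The declared one-sided 0.05 also does not match the planned 95% interval. That the calculation cannot be reproduced is certain; that the intended α was two-sided with continuity correction is an inference, though the best supported one.

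It would be wrong to conclude that the trial is too small. If the 34% and 4% hold and attrition is 10%, power is at least about 85% under each test in the table, so no patients need to be added. The practical consequence is confined to results with two-sided p between 0.05 and 0.10 in favour of conservative treatment, where the protocol does not settle whether the primary result is positive.

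**What to change.** Reconcile the Sample size and Data analysis sections, keeping 72 patients.

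- **Preferred.** State two-sided α 0.05, power 0.80, 34% vs 4%, continuity-corrected, 32 evaluable and 36 randomised per arm. Add to the Data analysis section that the primary conclusion is drawn from the two-sided test at 0.05 with its 95% interval. Say whether the test is continuity-corrected, and use an interval that agrees with it.
- **If one-sided 0.05 was truly intended.** Keep it, correct the justification by giving the power that 36 per arm delivers (about 91 to 96%, depending on the test), and specify a one-sided test for the primary endpoint with a matching 90% interval or one-sided 95% bound.

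Either choice costs a sentence or two and should be made before outcome data are examined. The only loss under the preferred option is the laxer one-sided threshold.

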## Discussion

This study is primarily designed to evaluate the effectiveness of conservative treatment of acute AT ruptures, using a functional bracing system, in reducing complications other than re-rupture. A comparison is made between this functional bracing system and a minimally invasive operative repair of acute AT ruptures. Both treatment options used in this comparison allow immediate full weight bearing so none of the patients is denied the purported advantage of a functional after treatment [2,5,21-24].

There have been randomized clinical trials on treatment of acute Achilles tendon rupture but the methodological rigour is often low. There is a need for more rigorous designed studies on AT rupture treatment as this subject is still very much under debate. By publishing our protocol we wish to show our care for a profound design and methodological quality of our protocol. Moreover, when the design of a study is published it will help to achieve transparency about why and how studies are undertaken. The publication of a study design may help to reduce the problem of publication bias, i.e. selective publication of positive associations and disregarding negative and weak associations, prevent unnecessary duplication of research efforts and duplicate publication [25]. To our knowledge, there has never been a design study published regarding treatment of AT ruptures. By making this design study we wish to contribute to more profound research on AT rupture treatment and prevent publication bias for this open-labelled randomized trial.
